## Assessment of Adverse Events (AE)

Participants are asked to report adverse events during treatment period and rate the discomfort of the eventual adverse events caused by their participation in the treatment. These questions will be administered to adolescents immediately after treatment.

During treatment, AE and SAR are registered by a clinician. All AE that occurs during the trial and which are observed by a clinician or reported by the subject will be registered regardless of whether they are assessed as related to the treatment of not. Assessment of causal relationship, severity (mild, moderate, severe), and whether the AE is considered to be an SAE will be made by the project investigator. For each AE/SAE, a description of the event is recorded, start date for the AE/SAE, planned actions, actions taken, causal relationship, and whether it is an AE or SAE. Serious Adverse Events (SAE) are reported to the sponsor within 24 hours of the investigator being informed of the SAE.

### Assessment of causal relationship

The principal investigator is responsible for determining whether there is a causal relationship between the AE/SAE and the treatment.

All AE can be categorized as either likely related, possibly related, or not related.

**Not related:**A clinical event that is reasonably considered not to be related to the intervention. The event is unlikely to be associated with the intervention and can be explained by an underlying medical condition or concomitant medication.

**Possibly related:**A clinical event that occurs within a reasonable time after the intervention has been administered. The event could be explained by the intervention, but there is insufficient information to determine the relationship. The event could also be explained by an underlying condition or medication.

**Probably related:**A clinical event that occurs within a reasonable time after the intervention has been administered. It is unlikely that the event can be attributed to an underlying condition or medication and is most likely caused by the intervention.

### Assessment of expected AE

Based on previous research adverse events are defined a priori as expected (see complete list below). ^45,52^ All other adverse events are defined as unexpected.

Expected Adverse events:

· Increased symptoms of psychological distress (e.g., low mood/anxiety)

· Thoughts about death or suicide

· Increased stress due to the workload of the treatment

· Worsening of well-being during the treatment period

· Increased fatigue

· More or less sleep

· Headache

· Feeling that the treatment is not helping

· Feeling doubtful about the treatment

· Decreased motivation for treatment

· Feeling of not understanding the treatment

· Feelings of shame or guilt when the treatment is not followed as planned

### Assessment of intensity

Each adverse event shall be classified as mild, moderate or severe.

**Mild:** The adverse event is relatively tolerable and transient in its nature but does not affect the subject’s normal life.

**Moderate**: The adverse event causes deterioration of function but does not affect health. The event can be sufficiently unpleasant and interferes with normal activities but does not completely obstruct them.

**Severe**: The adverse event causes deterioration of function or work ability or poses a health risk to the subject.

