## Definition: Serious Adverse Event (SAE)

Serious Adverse Event (SAE): Any untoward medical occurrence that at any dose requires inpatient hospitalization or prolongation of existing hospitalization, results in persistent or significant disability or incapacity, is life-threatening, or results in death.

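### As worded, every adverse event that meets the moderate intensity grade also meets the severe grade, and no rule says which one applies.

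*Protocol*

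**What the plan says.** Under Assessment of intensity the protocol requires a single choice: "Each adverse event shall be classified as mild, moderate or severe". Three definitions follow.

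- Mild: "The adverse event is relatively tolerable and transient in its nature", with normal life unaffected.
- Moderate: "The adverse event causes deterioration of function but does not affect health". A second sentence adds: "The event can be sufficiently unpleasant and interferes with normal activities but does not completely obstruct them".
- The highest of the three grades, severe, is defined in one sentence with alternative conditions: "The adverse event causes deterioration of function or work ability or poses a health risk to the subject".

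Assessment of Adverse Events (AE) names who decides: "Assessment of causal relationship, severity (mild, moderate, severe), and whether the AE is considered to be an SAE will be made by the project investigator". The same section has a description recorded for each event. Seriousness is defined separately, under Definition: Serious Adverse Event (SAE), by outcomes such as an event that "requires inpatient hospitalization or prolongation of existing hospitalization". No section says which grade is given when an event fits two definitions.

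**The concern.** Three ordered grades work only if each event fits one of them. Here loss of function appears in both upper grades. In moderate it is combined with the absence of a health effect. In severe it is one of several alternatives, each sufficient by itself, and no degree of loss is attached to it.

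Take an adolescent whose increased fatigue reduces functioning at school without any risk to health. The moderate text fits, and so does the severe text. One careful grader may choose the closer description and record moderate. Another may choose the highest grade that applies and record severe. Both follow the protocol.

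What is at stake is the description of harm. Several events listed in Assessment of expected AE (fatigue, changed sleep, stress from the treatment workload) could impair function without affecting health. For such events a reader of the results could not tell what a severe grade meant, or reproduce the grading from the protocol.

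**Working it through.** There is no stated figure to reproduce. The check is a logical one on the three definitions.

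**Inputs**, all from Assessment of intensity:
- F: function deteriorates.
- W: work ability deteriorates.
- H: health is affected or at risk.

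**Rules as written**
- Moderate = F and not H.
- Severe = F or W or H.

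**All eight combinations**

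| F | W | H | Moderate met? | Severe met? | Result |
|---|---|---|---|---|---|
| no | no | no | no | no | neither |
| no | no | yes | no | yes | severe only |
| no | yes | no | no | yes | severe only |
| no | yes | yes | no | yes | severe only |
| yes | no | no | yes | yes | both |
| yes | no | yes | no | yes | severe only |
| yes | yes | no | yes | yes | both |
| yes | yes | yes | no | yes | severe only |

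The counts are 1 neither + 5 severe only + 2 both + 0 moderate only = 8. The two double-graded rows are exactly those with F and without H.

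**Does moderate's second sentence remove the overlap?** Let C mean that normal activities are completely obstructed. If the second sentence is binding, moderate becomes F and not H and not C. Severe is still F or W or H, because it does not mention obstruction. An event with F, without H and without C meets both. The sentence takes complete obstruction out of moderate, but it does not take partial obstruction out of severe.

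**Does it matter that affecting health and posing a health risk are not quite the same?** No. Moderate requires F, and F alone satisfies severe, so moderate is contained in severe however H is defined.

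**Size.** Let s be the share of events that are severe only, and p the share that impair function without affecting health. If double-graded events are called moderate, the severe share is s. If they are called severe, it is s + p. The difference is p. The protocol gives no frequencies by type of event, so p is unknown. The figure of two in eight counts combinations and is not an estimate of p.

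**The case against.** The best defence is that the intent can be recovered. The grades are ordered, one must be chosen, and moderate's wording about incomplete obstruction signals where the next grade should start. A single role, the project investigator, does the grading, so there is no spread across many raters. Each event also has its description, causality, expectedness and the actions taken, and adolescents rate discomfort themselves. No hypothesis or planned test uses intensity, and how events are tabulated may be left to an analysis plan that is not shown.

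Most of this stands, and it limits the consequence. It does not settle the grade: the boundary hinted at in moderate is absent from severe, and one grader still needs a rule. Nor is this a detail left for later, since the protocol fixes the definitions that apply while events are being graded.

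A reader might infer more than the documents support:

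- *That moderate can never be used.* It is contained in severe, but it would fall out of use only if the highest applicable grade always won, and no such rule is written.
- *That the whole severe count is arbitrary.* Events with a health risk, and those that reduce work ability alone, fit severe and nothing else.
- *That the overlap biases the comparison between arms.* The Blinding section names participants, therapists and the project manager as unblinded and does not state the project investigator's status. Any unmasked grading would be a separate matter.
- *That serious event reporting is compromised.* It has its own criteria and does not depend on intensity.

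**Conclusion.** The point holds in limited form. The moderate and severe definitions overlap for every event that impairs function without affecting health, and the protocol asks for one grade without saying which prevails. This is a rule stated wrongly rather than a missing detail, and it is cheap to correct.

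The effect is confined to the descriptive grading of harm. The primary and secondary analyses do not use intensity. How many events are concerned cannot be said from the protocol. The conclusion assumes that the word or in the severe definition is read in its ordinary sense, as making each condition sufficient. It also treats work ability as distinct from function, as the wording does.

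**What to change.** Reconcile the two definitions so that each event meets only one grade. The most direct way is to state in the severe definition the degree of functional loss that separates it from moderate; moderate already says that activities are not entirely blocked. The sponsor should choose the threshold. The sponsor should also say how reduced work ability is graded, because that condition is now unambiguously severe and a rewording could move it unintentionally.

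Apply the reconciled definitions to all events. Re-grade any already logged from their recorded descriptions, by someone masked to arm where feasible, so that the correction does not itself introduce a judgement made with knowledge of allocation.

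The cost is a one-sentence edit and a re-read of the event log. Some events may change grade.

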## **Table 3.** Content of the adolescent program in POET Treatment

| **Module** | **Name and theme of module** | **Content** |
| --- | --- | --- |
| Module 1 | Understanding how emotions work | - Psychoeducation about emotions, functionality of emotions, and emotion regulation and their relationship to mental health problems. - Introduction to fictive example characters. - Introduction to the Process model of emotion regulation. - Homework: Register emotions and identify vulnerability/resilience factors. |
| Video-link session: | Follow-up session | - Goal formulation (specific, measurable, assignable, realistic, and time-related goals). - Address any motivational problems. - Addressing adolescent´s vulnerability/resilience factors. |
| Module 2 | Feeling better by changing or modifying the situation | - Repetition module 1 and review homework. - Addressing unhelpful avoidance. - Information on how to stay in or seek out situations that are usually avoided and how to seek out positive situations. - Homework: Reduce vulnerability factors, stay in situations that usually are avoided or seek out positive situation. |
| Module 3 | Feeling better by focusing on your emotions | - Repetition module 2 and review homework. - Psychoeducation about the components of emotions and addressing emotional awareness. - Homework: Practicing identification of emotions. |
| Module 4 | Feeling better by letting go of or changing your thoughts | - Repetition module 3 and review homework. - Psychoeducation about thoughts, addressing common negative beliefs about emotions and emotion regulation. - Psychoeducation about mindful observations, acceptance of thoughts, and helpful appraisal styles. - Homework: Practicing mindful observation, acceptance of thoughts, and helpful appraisal styles. |
| Module 5 | Feeling better by changing your behaviors | - Repetition module 4 and review homework. - Psychoeducation about behaviors and impulses, addressing impulsivity. - Engage in alternative behaviors in situations when one typically acts impulsively. - Homework: Engage in alternative behaviors instead of engaging in impulsivity. |
| Module 6 | Summary | - Repetition module 4 and review homework. - Summary and maintenance plan. |

## **Table 4.** Content of the parent course in POET Treatment

| **Module** | **Name and theme of module** | **Content** |
| --- | --- | --- |
| Module 1 | Emotions and emotion regulation | - Introduction to emotion regulation and the role of parents during the treatment period. - Introduction to fictive parent characters. - Homework: Supporting the adolescent handling vulnerability/resilience factors. |
| Video-link session: | Follow-up session | - Goal formulation (specific, measurable, assignable, realistic, and time-related goals). - Address any motivational problems. - Addressing adolescent´s vulnerability/resilience factors. |
| Module 2 | Supporting adolescents in developing adaptive skills concerning different situations | - Repetition module 1 and review homework. - Addressing unhelpful avoidance. - Introduction to shared parent-adolescent time. - Introduction to strategies for parents to support their adolescents in facing avoided situations and seeking positive experiences. - Homework: Engage in shared parent-adolescent time and supporting adolescents to stay in situations that are avoided or seek out positive situations. |
| Module 3 | Validation | - Repetition module 2 and review homework. - Introduction to the concept of validation. - Homework: Engage in shared parent-adolescent time and validation. |
| Module 4 | Supporting adolescents in developing adaptive skills to manage their thoughts | - Repetition module 3 and review homework. - Introduction to common pitfalls when practicing validation. - Introduction to how parents can support their adolescent in changing their attitude toward their thoughts. - Homework: Engage in shared parent-adolescent time, validation, and supporting their adolescent with acceptance of thoughts and helpful appraisal styles. |
| Module 5 | Supporting adolescents in developing adaptive skills to manage impulsivity and manage conflicts | - Introduction to conflict management and collaborative problem-solving. - Homework: Practice collaborative problem-solving. |
| Module 6 |  | - Summary and maintenance plan |

## **Table 5.** Content of the adolescent program in Supportive Treatment

| **Module** | **Name and theme of module** | **Content** |
| --- | --- | --- |
| Module 1 | Receiving support | - Introduction to mental health. - Reflection on the type and level of support the adolescent needs from oneself and others. - Introduction to fictive characters. - Homework: Reflect on their well-being and mental health problems. |
| Video-link session: | Follow-up session | - Address any motivational problems with adolescent. - Addressing direction for the treatment by reflecting on the “What does improved well-being mean to you?”. |
| Module 2 | Self-esteem, self-confidence, and identity | - Repetition module 1 and review homework. - Introduction to self-esteem, self-confidence, and identity. - Psychoeducation about common mental health problems. - Homework: Reflect on their self-esteem, and self-confidence during the week and how it can be strengthened. |
| Module 3 | Friendships | - Repetition module 2 and review homework. - Psychoeducation about the reasons (genetics, environment) for having common mental health problems. - Introduction to and reflection on friendship and how it can affect one’s mental health. - Homework: Reflect on what defines a good friendship, how they can handle bad relationships and how to find new friends. |
| Module 4 | Family | - Repetition module 3 and review homework. - Psychoeducation about how mental health problems are manifested physically (e.g., headaches, digestive problems, and fatigue). - Introduction to and reflection on family problems and how they might affect one´s mental health. - Homework: Reflect on how the family affects one´s mental health and how to make the best of one´s family situation. |
| Module 5 | School | - Repetition module 4 and review homework. Psychoeducation on reasons for developing mental health issues. - Introduction to and reflection on school and how school might affect one´s mental health. - Homework: Reflect on what can be done in school to positively impact their mental health and how to manage school stress. |
| Module 6 | Summary | - Repetition module 5 and review homework. - Summary and maintenance plan. |

## **Table 6.** Content of the parent course in Supportive Treatment

| **Module** | **Name and theme of module** | **Content** |
| --- | --- | --- |
| Module 1 | Supporting adolescents in reflecting on receiving support | - Introduction to mental health problems in youth the role of parents in treatment. - Reflection on the types of mental health problems affecting their adolescent. - Introduction to fictive parent characters - Homework: Reflect on what could be done to improve the well-being of their adolescent. |
| Video-link session: | Follow-up session | - Address any motivational problems with - adolescent and parent. |
| Module 2 | Supporting adolescents in reflecting on self-esteem, self-confidence, and identity | - Repetition module 1 and review homework. - Introduction to and reflecting on being a parent to an adolescent. - Homework: Reflect on the challenges they experience in parenting and on how to strengthen their adolescent’s self-esteem. |
| Module 3 | Supporting adolescents in reflecting on friendship | - Repetition module 2 and review homework. - Introduction to and reflecting on their adolescent safety net. - Introduction to and reflection on their adolescent´s internet use. - Homework: Reflect on how they can support their adolescent's friendships. Reflect on concerns about their adolescent’s internet use. |
| Module 4 | Supporting adolescents in reflecting on family relations | - Repetition module 3 and review homework. - Introduction to and reflecting on their adolescent family relations. - Introduction to and reflection on self-care activities. - Homework: Reflect on actions to take to improve family relationships, and self-care activities for themselves. |
| Module 5 | Supporting adolescents in reflecting on school | - Repetition module 4 and review homework. - Introduction to and reflection on how school might affect one´s mental health. - Homework: The parent is encouraged to reflect on their adolescent school situation and self-care activities for themselves. |
| Module 6 | Summary | - Repetition module 5 and review homework. - Summary and maintenance plan. |

